### 2.10. fNIRS

The cortical activation level during gait will be recorded by a portable multi-channel frequency domain fNIRS system (BRITE, Artinis Medical Systems, Gelderland, The Netherlands). The particular regions of interest are the motor cortex (M1), supplementary motor cortex (SMC), and premotor cortex (PMC). The system consists of 28 optodes and is made up from 12 light source fibers and 16 detector fibers, giving 42 recording channels. The optode distance will be set at 3.0 cm and will be located over the bilateral fronto-parital cortices, including the primary supplementary, premotor cortices, prefrontal cortices, and sensorimotor area. The changes in the oxygenated hemoglobin concentration level will be recorded at rest and during 30 s of walking for five repetitions. 

### 2.11. Outcome Assessments

Each centre has a dedicated multidisciplinary assessment team who are specifically trained to deliver the outcome assessments. Team members consist of occupational therapists, physiotherapists, physicians, and nurses who will be blinded to the group allocation. 

### 2.12. Sample Size

Sample size calculation will be based on the primary outcome measures of gait speed. An increase in gait speed of 0.16 m/s has been stated as the minimal clinically significant difference in the first 60 days of stroke occurrence [54] that correlating with a meaningful improvement in disability level post intervention. The study will consider 0.3 m/s for power calculation since other study-reported changes below this value are likely to be measurement errors [55].

The sample size was determined using the sample size calculator G*Power. The calculation model is based on the F test family, the statistical “ANOVA: Repeated measures, between factors” test and the “A priori: Compute required sample size–given alpha power, and the effect size” as the power analysis type. Power calculation was based on a mean difference of 0.3 (mean of group 1 = 0.69; mean of group 2 = 0.39) and the standard deviance of each group of 0.75 with a total sample population of 60. A total of 206 participants (103 in each group) is required to provide 95% power and an effect size of 0.2. Taking a 10% missing rate into consideration, a final sample size of 226 participants (113 in each group) was determined. 

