### 4.2. Data Analysis

All statistical analyses will be performed in IBM SPSS version 21 software (SPSS Inc., Chicago, IL, USA). Descriptive statistics will be conducted to describe the sample population. The demographic characteristics and baseline results for the primary and secondary outcome measures will be analyzed using analysis of variance (ANOVA) or Chi-square test for categorical data. A mixed-effect model analysis will be adopted to compare changes in all of the outcome measures between groups at the completion of the intervention and at the 3- and 6-month follow-ups. The mixed-effect model analysis will include treatment, time, and centre as fixed effects, and the participants will be included as the random effect. Changes in the outcome measures will be adjusted for age, sex, centre, and time. The level of statistical significance will be set at *p* < 0.05. Cohen’s d will be calculated to measure the effect size of the difference for every comparison. The effect size will be interpreted as follows: 0.2—small effect size; 0.5—medium effect size; and 0.8—large effect size. Stratification analysis will be conducted to explore the potential effect difference between centres. There are no planned interim analyses or stopping rules, as the power calculation has accounted for loss to follow-up. In the event of missing data during the follow-up period, the modified intention to treat principle will be followed with the last observation carried forward method. 

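### The 95% power for 206 patients applies to a group difference averaged over several measurements; for one planned time point the same inputs give about 82% at an assumed correlation of 0.5, with a wide range.

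*Protocol article*

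**What the plan says.** All of the power inputs are in section 2.12 of the protocol article. The test chosen in G*Power is "ANOVA: Repeated measures, between factors". The effect is given as "Power calculation was based on a mean difference of 0.3 (mean of group 1 = 0.69; mean of group 2 = 0.39"), with "the standard deviance of each group of 0.75 with a total sample population of 60". The result is "A total of 206 participants (103 in each group) is required to provide 95% power and an effect size of 0.2". The allowance for loss follows: "Taking a 10% missing rate into consideration, a final sample size of 226 participants (113 in each group) was determined". The number of measurements and the correlation between them are not given.

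Section 2.7.2 schedules four assessments: baseline, post-intervention, and 3 and 6 months post-intervention. The last paragraph of the Introduction hypothesises superiority right after the two weeks of treatment and at both follow-ups. Section 4.2 says a mixed-effect model will "compare changes in all of the outcome measures between groups at the completion of the intervention and at the 3- and 6-month follow-ups". Its fixed effects are treatment, time and centre, with participant as the random effect. Adjustment is for age, sex, centre and time. Baseline gait speed is not listed.

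**The concern.** The between-factors option answers one question: do the groups differ on the average of all repeated measurements, given a constant difference at each? Averaging reduces the variance, so this test needs fewer patients than a comparison at one visit. The aims and the analysis section name three separate post-baseline comparisons of change. If the 95% is read as applying to each of them, the risk of missing a true 0.3 m/s effect is understated, and a null result at one visit would be taken as stronger evidence of no effect than the inputs allow.

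A second, smaller matter is the attrition line. The number randomised appears to be the required number times 1.1, which does not return the required number after a 10% loss.

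**Working it through.** **Inputs.** Difference 0.3, SD 0.75, total N 206 (103 per arm), power 95%, missing rate 10% (section 2.12); significance level 5% (section 4.2), taken as two-sided; 1:1 allocation (section 2.5); four scheduled visits (section 2.7.2). The number of measurements m and the correlation rho are assumptions, because the article gives neither.

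**Effect size.** d = 0.3/0.75 = 0.4 and f = d/2 = 0.2, as stated.

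**Reproducing 206.** For the between-factors test, lambda = f² × N × m / (1 + (m − 1) × rho), referred to a noncentral F with 1 and N − 2 degrees of freedom.
- m = 4, rho = 0.5: lambda = 0.04 × 206 × 4 / 2.5 = 13.18, power 95.1%. N = 204 gives 94.9%, so 206 is the smallest even N.
- At rho = 0.5, other values of m need a different N for 95%: m = 3 needs 220, m = 2 needs 246, m = 1 needs 328.
- 206 also results from m = 3 with rho = 0.44 and from m = 2 with rho = 0.25.

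With a single measurement, 206 gives 81.5%. Under the stated f, 95% is reached only by averaging over more than one measurement.

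**One time point, raw values.** Noncentrality = 0.4 × √(103/2) = 2.87. Power is 81.5% (t) or 81.9% (normal approximation). A power of 95% would need 164 per arm.

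**One time point, change from baseline.** If 0.75 is the SD of raw gait speed, the SD of change is 0.75 × √(2(1 − rho)).

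| rho | SD of change | Power, 103 per arm |
|---|---|---|
| 0.3 | 0.887 | 68% |
| 0.5 | 0.750 | 82% |
| 0.6 | 0.671 | 89% |
| 0.7 | 0.581 | 96% |

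**One time point, baseline as covariate.** The SD is 0.75 × √(1 − rho²). Power is about 85% at rho 0.3, 91% at 0.5 and 98% at 0.7.

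**Average of the three post-baseline visits, rho = 0.5.** lambda = 0.04 × 206 × 3 / 2 = 12.36, power 93.8%.

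**Average of four visits with no expected baseline difference, rho = 0.5.** The average difference is 0.3 × 3/4 = 0.225, so f = 0.15 and lambda = 0.0225 × 206 × 4 / 2.5 = 7.42. Power is about 77%.

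**Attrition.** 206 × 1.1 = 226.6, which matches the stated 226 rounded down. 226 × 0.9 = 203.4. Keeping 206 needs 206/0.9 = 228.9, that is 229, or 230 for equal arms. With 203 patients, the m = 4, rho = 0.5 model gives 94.8% against 95.1%.

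**Power with 203 evaluable.** One time point, raw or change at rho 0.5: about 81% (change: 67% at rho 0.3, 96% at 0.7). Baseline-adjusted at rho 0.5: about 90%. Pooled over three post-baseline visits at rho 0.5: about 93%.

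**The case against.** The strongest reply is that section 4.2 lists treatment, time and centre as fixed effects and no treatment-by-time term. Read literally, that model yields one treatment effect pooled over visits, the kind of quantity a between-factors calculation addresses. Pooled over the three post-baseline visits, power is about 94% at correlation 0.5, one point below the claim. This stands as a possible reading. It does not settle the matter, because the Introduction and the same section 4.2 name each of the three times as a comparison, and the article does not say which one carries the 95%.

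A reader might infer that the 95% certainly rests on four visits including baseline, and so on a 0.3 m/s difference before treatment. The article does not establish this. Four measurements with correlation 0.5 is the most natural reconstruction because it matches the visit schedule, but other pairs also give 206. The 77% figure is conditional on that reading.

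A reader might also infer that the true miss risk for each planned comparison is about 18%. That holds for raw values or for change at correlation 0.5. The correlation is not given, and over 0.3 to 0.7 the power for change runs from well below 82% to slightly above 95%. A high correlation does not rescue the stated calculation, though: at 0.7 the four-measurement model itself falls to 90% with 206.

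On attrition, the shortfall is three patients (four for equal arms) and costs about 0.3 points of power. Section 4.2 also carries the last observation forward, so some patients with missing follow-up would stay in the analysis, and 203 is a cautious count. It is fair to call this minor.

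Finally, a condensed article may leave m and rho to the full protocol. Their absence alone would not be a finding. What remains is a stated 95% that is not tied to the comparisons the same article plans.

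**Conclusion.** The point holds in limited form. The 95% is a property of an average over several measurements and is not supported as the power of a comparison at end of treatment, 3 months or 6 months. Under the article's difference and SD, one such comparison with 103 per arm has about 82% power on raw values or on change at correlation 0.5; for change it ranges from 68% to 96% over correlations of 0.3 to 0.7. If the pooled post-baseline effect is meant, the figure is about 94% at correlation 0.5 and the discrepancy is small. These figures assume a two-sided 5% test, a constant 0.3 m/s effect after baseline, and that 0.75 is the SD of gait speed at one visit.

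It does not follow that the trial is too small: at the middle correlation, per-visit power still exceeds 80%. The attrition line is wrong arithmetically but of little consequence. Severity: should-fix.

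**What to change.** Keep 226 and revise section 2.12:

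1. State the number of measurements and the correlation entered in G*Power, and whether baseline was one of the measurements.
2. Say which comparison the power refers to: one named time point or the effect pooled over the post-baseline visits. The article names no primary time point, so one would have to be designated before a per-visit figure is quoted as the trial's power.
3. Restate the power for that comparison. With about 203 evaluable and correlation 0.5, it is about 81% per time point, with the range over plausible correlations, or about 93% for the pooled post-baseline effect. A figure of about 90% per time point may be quoted only if baseline gait speed is added to the covariates in section 4.2.
4. Correct the attrition sentence: 226 with 10% missing leaves about 203. If 206 is to be kept, 229 are needed, or 230 for equal arms.

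The cost is text only. The stated power becomes less favourable; no extra patients are needed unless the sponsor prefers 230. Adding baseline as a covariate would be a change to the analysis and should be made before the data are unblinded.

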## 3. Procedure

The Standard Protocol Items: Recommendations of Interventional Trials (SPRIT) figure illustrates the overview of the schedule of all events of the study (Table 2). 

### 3.1. Control Group 

The Participants in the control group will receive conventional rehabilitation treatment and routine medical care. Conventional rehabilitation programs include physiotherapy and occupational therapy. The program includes muscle strengthening exercises, treadmill or over ground gait training exercise, balance training such as body weight transfer, upper limb training such as passive range of movement and foam rolling, and functional practice of daily living activities such as object transfer, peg hole exercises and object manipulation, and neuromuscular electrical stimulation. Rehabilitation will be provided 5 days a week for 2 weeks. The daily duration of all of the rehabilitation components will last for a total of 2 h. Table 3 presents the time allocation for each training item.

### 3.2. Intervention Group

The intervention group will receive interlimb-coordinated training for 20 min in addition to conventional training. Each of the conventional rehabilitation components will be shortened to reduce the overall conventional therapy program duration for a total of 20 min in the intervention group. This is to give equivalent therapeutic time among the two groups. Interlimb-coordinated training will be conducted on a bespoke bi-cycle ergometer where participants will be asked to perform arm and leg cycling simultaneously. A diagram of the bespoke bi-cycle ergometer is illustrated in Figure 3. The 20 min of interlimb-coordinated training will be divided into 10 min of active cycling and 10 min of active-assisted cycling. In active-assisted mode, the participants will be asked to primarily lead the movement with the paretic side, and assistance will be provided by the ergometer’s motor, which reduces the effort required from the participant. The bespoke bi-cycle ergometer is designed to have a separate motor on the left and right sides to ensure that assistance is only provided to the paretic side. In active cycling mode, the four motors that power the handlebars and pedals are linked to enable a synchronized reciprocal cycling motion of the upper and lower limbs simultaneously. Participants will be asked to cycle at a work rate that would provide a score of between 10–13 (light–somewhat hard) on the Borg’s Rating of Perceived Exertion scale [56]. The exact work rate on the cycle ergometer could not be pre-determined or fixed for every participant, as each participant is likely to have a different exercise capacity. Thus, a subjective Borg scale was adopted as an index to monitor work rate intensity. 

## 4. Safety and Adverse Event Reporting

Patients with acute stroke have a likelihood of morbidity and mortality. Procedures are in place to minimize the occurrence of adverse events. Medical doctors will assess participants to ensure safe rehabilitation participation. Medically unstable patients will not be recruited for the study. Participants will be asked to exercise according to their physical capability. Trained physiotherapists/occupational therapists who work closely with the inpatient clinical team will be onsite during the exercise sessions. Any issues raised during the exercise session will be reported to the inpatient medical team. The following safety reporting procedures are in place:Serious adverse events (SAEs) are defined as an event that incurs harm to the participants, which may or may not require medical or surgical intervention as a preventative measure to avoid the following outcomes: death, further impairment of body function, damage to a body structure, and prolonged the hospitalization period.All SAEs related to the interventions will be recorded on a SAEs event report form in accordance with the procedures of each research centre.All of the SAEs related to the interventions must be reported to the Principal Investigator within 24 h of learning of the event.SAEs that are related to the interventions will be reported to the University Clinical Trial Unit and Research Ethics Committee within 15 days of the occurrence of the SAEs. The following information will be reported to relevant parties: (1) the concerned research protocol; (2) a report on the description of the SAE and subsequent outcome; (3) a proposal of changes in response to the SAE to prevent further occurrence of SAEs

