### 2.2. Study Setting

Data collection will take place at the rehabilitation department of four tertiary hospitals located in different regions of China: (1) The First Affiliated Hospital of Sun Yat-Sen University; (2) The Seventh Affiliated Hospital of Sun Yat-sen University; (3) The Fifth People's Hospital of Foshan Institute of Science and Technology; and (4) the Beijing Rehabilitation Hospital of Capital Medical University. Participants will be recruited from the inpatient wards of the participating centers. The data collection process is expected to last for 4 years. All interventions will be delivered by trained healthcare professionals within these centers. Figure 1 shows the study procedure. 

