### 2.6. Ethics

Ethical approval was obtained from the Medical Ethical Committee of the First Affiliated Hospital of Sun Yat-Sen University (Ethics Number: [2020]430). The clinical trial is registered with the Chinese Clinical Trial Registry (Registration Number: ChiCTR2000040137, prospective registration on the 22 November 2020). All relevant parties will be informed of any important modifications to protocol modifications. All of the participants who are invited to participant in the study will be given time to consider if they wish to take part in the trial and will be encouraged to ask any questions. All of the participants will be free to withdraw from the trial at any time without providing a reason. The participants will be able to withdraw themselves completely, in which case, all of the collected data will be excluded from the study, or to withdraw only from further assessment or intervention, in which case, all of the collected data will be included in the final analysis depending on personal preference. Medical expenses that are incurred as part of the research are covered by the research grant. Travel reimbursement will also be provided to all participants during the follow-up periods to promote a strong adherence rate. 

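### The SAE definition sets no seriousness threshold, and its outcome list omits new hospital admission, so the four centres can classify the same event differently

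*Protocol article*

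**What the plan says.** The definition is in section 4 (Safety and Adverse Event Reporting). It opens with "Serious adverse events (SAEs) are defined as an event that incurs harm to the participants", continues "which may or may not require medical or surgical intervention as a preventative measure to avoid the following outcomes", and then lists "death, further impairment of body function, damage to a body structure, and prolonged the hospitalization period".

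The same section sets out what follows from the classification:
- "All SAEs related to the interventions will be recorded on a SAEs event report form", and this is done under the procedures of the individual centre.
- Related SAEs "must be reported to the Principal Investigator within 24 h of learning of the event".
- Related SAEs go to the clinical trial unit and the ethics committee within 15 days of occurrence.

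On setting and follow-up:
- Section 2.2 says "Participants will be recruited from the inpatient wards of the participating centers", and names four hospitals.
- Section 3.1 gives a programme of 2 weeks.
- Section 2.7.2 places the later assessments at 3 and 6 months after the intervention.
- Section 2.6 adds "Travel reimbursement will also be provided to all participants during the follow-up periods".

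**The concern.** A definition of seriousness has to separate serious harm from minor harm, and here the clause that should do so is worded so that it cannot. The listed outcomes enter the sentence only as things an intervention might avert, not as criteria in their own right. A site that wants a workable rule must rewrite the sentence for itself, and two rewrites are open to it. One takes in all harm. The other uses the list, which has a gap for hospital admission.

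What is at stake is safety reporting. SAE reporting is the only structured safety measure the article describes; neither the outcome sections (2.7.1 and 2.7.2) nor Table 1 lists a safety outcome. The classification decides which related events go to the principal investigator within 24 h and to the trial unit and ethics committee within 15 days. If centres differ, those reports, and any SAE count later drawn from them, mix different kinds of event.

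**Working it through.** No arithmetic applies: the article gives no SAE rate, and the point rests on wording. The check is to read the definition clause by clause against the setting and the follow-up.

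**1. The opening criterion.** "Serious adverse events (SAEs) are defined as an event that incurs harm to the participants" sets no degree of harm. Transient muscle soreness after cycling would meet it.

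**2. The qualifying clause.** "which may or may not require medical or surgical intervention as a preventative measure to avoid the following outcomes" covers events that need intervention and events that do not. Those two groups together are all events, so the clause removes none. The definition reduces to step 1.

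**3. The list as the test.** Suppose a site ignores the qualifier and uses the four outcomes as criteria.

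| Listed outcome | Can it apply after discharge? |
|---|---|
| Death | Yes |
| Further impairment of function | Yes |
| Structural damage | Yes |
| Prolonged hospital stay | No, it presupposes a current stay |

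The wording of the last items is "damage to a body structure, and prolonged the hospitalization period". New or repeat admission does not appear. The term life-threatening does not appear either, although an event needing intervention to avoid death comes close to it in substance.

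**4. When the gap can matter.** Participants are recruited as inpatients and treated for 2 weeks, then seen at 3 and 6 months after the intervention. Reimbursed travel suggests that most will be at home by those visits, but no discharge date is given, so this is an inference. For anyone discharged, the hospital item has nothing to act on and the other three outcomes remain.

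**5. The relatedness filter.** Recording and both reporting deadlines cover only SAEs related to the interventions. The literal reading therefore brings in minor harm judged related to training. The list reading leaves out an admission judged related that causes no death, further impairment or structural damage, and that a site does not count as averting one of these.

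**6. A common rule.** The article refers recording to each centre's procedures and states no rule that chooses between the two readings. The four centres can therefore apply different ones.

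**The case against.** The strongest reply is that the literal text errs only towards too much reporting. A definition that covers any harm also covers a re-admission for harm, so nothing is missed. This is right for the literal reading. It does not rescue the sentence, because a site that finds that reading unworkable is left with the list, and the list has the gap. The two faults belong to alternative readings and are not claimed to occur together.

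A reader might infer more: that the definition fails once participants leave hospital, or that it misses a recurrent stroke or a fracture. The article does not support this. Three of the four outcomes do not depend on being an inpatient. A fracture is structural damage, and a recurrent stroke would ordinarily bring further impairment. Follow-up is also counted from the end of the intervention, not from discharge.

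Three further replies have weight:
- The relatedness filter, not the list, would often decide whether a late event is recorded. This stands, and it narrows the gap to admissions judged related.
- Section 4 has another channel: problems during an exercise session go to the inpatient medical team. It covers sessions only and does not classify events.
- The article is condensed, and the report form and centre procedures are not shown. They may contain a sounder rule. The point remains, because the article states a definition and what it states is defective.

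**Conclusion.** The point holds as a defect of wording with practical consequences. The qualifier removes the seriousness threshold. The fallback list names prolonged hospitalisation but not new or repeat admission, and does not name life-threatening events; the second omission is largely one of terminology. Classification is left to each site.

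No number can be attached. The article gives neither an adverse event rate nor a discharge date, so any share of follow-up time or count of misclassified events would rest on invented inputs. The effect is confined to SAE classification, the 24 h and 15-day reports and any later SAE summary. Section 4.2 specifies no SAE analysis, and gait speed and the efficacy comparison are untouched. The conclusion assumes that no document outside the article already imposes one definition on all centres. The correction should be made.

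**What to change.** Replace the definition in section 4 with one in which the outcome is the criterion. An SAE would be an untoward event that does at least one of the following:
- results in death;
- is life-threatening;
- leads to a new hospital admission or prolongs an existing one;
- causes persistent or significant impairment, or structural damage;
- needs medical or surgical intervention to prevent one of these.

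Delete the clause that lets intervention be either required or not. State that this one definition applies at all four centres from allocation to the 6-month visit, whatever local recording procedures are used.

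The cost is one paragraph and a note to sites. Fewer trivial events should be classed as serious, and admissions judged related would be classed alike everywhere. The change does not alter the restriction to related events, so it will not by itself capture admissions judged unrelated.

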## 2. Materials and Methods 

### 2.1. Study Design

This study is a parallel, single-blinded, multi-center randomized controlled trial to evaluate the effect of interlimb-coordinated intervention on gait and motor function recovery in patients with acute stroke. 

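### Recording of a serious adverse event is conditional on its being judged related to the interventions, so any comparison of serious harms by arm is filtered by attribution

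*Protocol article*

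**What the plan says.** Section 4 (Safety and Adverse Event Reporting) of the protocol article first defines an SAE by harm and outcome, without reference to cause. It then sets three steps, each limited by relatedness:

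- Recording: "All SAEs related to the interventions will be recorded on a SAEs event report form", following each centre's own procedures.
- Notice to the Principal Investigator: "All of the SAEs related to the interventions must be reported to the Principal Investigator within 24 h of learning of the event".
- External report: "SAEs that are related to the interventions will be reported to the University Clinical Trial Unit and Research Ethics Committee within 15 days".

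For lesser events the section says: "Any issues raised during the exercise session will be reported to the inpatient medical team". It states no research record for them.

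The same section acknowledges a background of serious events: "Patients with acute stroke have a likelihood of morbidity and mortality". On staffing it says: "Trained physiotherapists/occupational therapists who work closely with the inpatient clinical team will be onsite during the exercise sessions".

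On blinding, Section 2.1 states: "This study is a parallel, single-blinded, multi-center randomized controlled trial". Section 2.11 describes the outcome assessment teams as blinded. No other role is described as blinded, and no one is named as deciding relatedness.

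**The concern.** Limiting expedited notices to related events is a common choice. Limiting recording is different, because the relatedness judgement then decides whether a serious event appears in the safety record at all.

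Where serious events are expected from the disease itself, as Section 4 accepts, it is hard to attribute a single case with confidence. Comparing all events by randomised arm is the safeguard, because it needs no judgement of cause. The stated rule does not provide for that comparison.

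This matters here for three reasons. The introduction says it is unclear whether the intervention can be used in the acute phase, and the discussion promises evidence on feasibility as well as efficacy, so serious harms by arm bear directly on the trial's aims. Recording follows each of four centres' own procedures, so the threshold for calling an event related may differ between them. And Section 4.2 plans no interim analysis or stopping rule, so the final safety comparison carries most of the weight.

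**Working it through.** The article states no figure on this point, so there is nothing to reproduce. The check is a reading of the text, followed by an illustration of how the filter acts.

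**Text**

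1. Is the condition attached to recording, or only to expedited reporting? To both. The recording sentence carries it in its own right.
2. Does any other section provide for SAEs whatever their cause? No. Section 4.1 mentions a case report form and a central data system but does not list their content. Section 4.2 describes no safety analysis.
3. Does the condition exclude the control arm? Not necessarily. The wording is plural, and Table 2 lists both the interlimb programme and routine rehabilitation under interventions. Related SAEs could be recorded in both arms.
4. Who judges relatedness? Not stated. Therapists on site can see whether the ergometer is used. The blinded teams in Section 2.11 include physicians and nurses, so a blinded judgement is not ruled out.

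**Illustration**

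The number per arm, 113, is from Section 2.12. The SAE risks and the probabilities of being judged related are assumptions; the article gives neither.

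Expected recorded SAEs in an arm = 113 × SAE risk × probability of being judged related.

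Equal true risk in both arms (C = control, I = intervention):

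| SAE risk | SAEs per arm | Judged related, C / I | Recorded, C / I | Unrecorded, of total |
|---|---|---|---|---|
| 5% | 5.65 | 10% / 10% | 0.6 / 0.6 | 10.2 of 11.3 |
| 5% | 5.65 | 10% / 50% | 0.6 / 2.8 | 7.9 of 11.3 |
| 10% | 11.3 | 10% / 10% | 1.1 / 1.1 | 20.3 of 22.6 |
| 10% | 11.3 | 10% / 30% | 1.1 / 3.4 | 18.1 of 22.6 |
| 10% | 11.3 | 10% / 50% | 1.1 / 5.7 | 15.8 of 22.6 |
| 20% | 22.6 | 10% / 10% | 2.3 / 2.3 | 40.7 of 45.2 |
| 20% | 22.6 | 10% / 50% | 2.3 / 11.3 | 31.6 of 45.2 |

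Worked for the 10% risk, 10% / 50% row: control 113 × 0.10 × 0.10 = 1.13; intervention 113 × 0.10 × 0.50 = 5.65; unrecorded 22.6 − 1.13 − 5.65 = 15.8.

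The filter also works the other way. The recorded ratio between arms is the true risk ratio multiplied by the ratio of attribution probabilities. Take true risks of 20% in intervention and 10% in control:

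- With 10% judged related in both arms, 22.6 versus 11.3 events become 113 × 0.20 × 0.10 = 2.26 versus 113 × 0.10 × 0.10 = 1.13. The ratio survives, but on too few events to see it.
- With 10% judged related in intervention and 20% in control, 2.26 versus 113 × 0.10 × 0.20 = 2.26 are recorded. The doubling disappears.

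Recording all SAEs gives the unfiltered counts in every scenario.

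**The case against.** The strongest reply is that a journal article condenses a fuller protocol. The case report form, the central data system and the centres' procedures are not shown, and any of them might capture unrelated events. The text also never says that related SAEs alone are to be recorded. This tempers the point but does not remove it: the article is not silent, it states a recording rule, and it repeats the same restriction in all three steps. A fuller document that recorded every SAE would be at odds with it.

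The reply does dispose of several stronger readings that a reader might infer:

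- That harms cannot be compared between arms at all. Related SAEs can be compared if the wording covers both arms, as Table 2 allows. What is missing is a comparison free of attribution.
- That unblinded staff make the judgement. This is plausible, since therapists see the ergometer, but no assessor is named.
- That unrelated events would be absent from the whole trial database. The article shows only that the SAE form does not provide for them.
- That the reasons for missing gait speed would be lost. An SAE form is not the only place to record them, and nothing shown says they go unrecorded.

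It is also fair to say that training is seated, at a light to somewhat hard perceived exertion, and replaces 20 of 120 minutes of daily therapy. That bears on how many harms to expect, not on whether they should be counted without a filter.

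**Conclusion.** The point holds in this form: as written, Section 4 makes relatedness the entry condition for the SAE record, under centre-specific procedures and with no stated assessor, criteria or blinding. SAEs judged unrelated are not provided for, and any comparison of serious harms by arm depends on attribution that may be unblinded.

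The size cannot be fixed from the document. Under the assumed values, at an equal 10% risk between about 16 and 20 of 22.6 expected SAEs would go unrecorded, and the recorded counts could range from 1.1 versus 1.1 to 1.1 versus 5.7. The numbers rest on those assumptions, but the mechanism does not: unless every SAE is judged related, events are lost, and unequal attribution between arms distorts the comparison. The sponsor should correct this; it does not affect the primary efficacy analysis as the article describes it.

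**What to change.** Change the recording sentence in Section 4 so that every SAE in both arms, from randomisation to the 6-month follow-up, is recorded on one form common to all centres, whatever its presumed cause. Make relatedness a separate field on that form, name who completes it and by what criteria, and have it judged blind to arm where feasible. State that all SAEs will be tabulated by randomised arm, with related SAEs as a subset. The 24-hour and 15-day notices may stay limited to related SAEs.

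The cost is an amendment of a few sentences and slightly more form completion at four sites. It is best made early, because events that were never recorded are hard to recover later.
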